## 10.4 Reporting of a Serious Breach

- The Principal Investigator must report a serious breach occurring at a participating site to the Coordinating Principal Investigator within a specified timeframe.
- The Coordinating Principal Investigator must review the serious breach, along with the clinical trial protocol, to develop a Corrective and Preventive Action (CAPA) that defines the steps to prevent the serious breach from reoccurring.
- The serious breach report and the CAPA must be provided to the approving HREC, and the UNSW sponsors delegate for review and approval.

## 10.5 Reporting of Serious Breaches by Third Parties

- A Suspected Breach is a report judged by the reporter as a possible serious breach but has yet to be formally confirmed as a serious breach by the sponsor.
- A Suspected Breach form must be completed when a third party (e.g., individual/institution) wishes to report a suspected breach of Good Clinical Practice or the protocol and should be reported directly to the reviewing HREC without reporting through the sponsor.
- Recording of Protocol Deviation and Serious Breach Reports
- A register of protocol deviation and serious breach reports must be recorded. Written records and copies of documentation sent to the sponsor must be retained in the Investigator Site File.
- Copies of protocol deviation and serious breach reports must be recorded, written records and copies of documentation sent to the sponsor, referrals made to the HREC or establishing whether a breach of the Australian Code for Responsible conduct of research must be retained in the Master Site File.

## 11. Review of a Protocol Deviation and a Serious Breach

- The UNSW Sponsor's Delegate will review reports to establish whether the event meets the definition of a protocol deviation or serious breach, establish whether the proposed CAPA is appropriate and establish whether there is or will be ongoing impact reliability and robustness of the data generated.
- The UNSW Sponsor's Delegate will seek advice from the approving HREC on the corrective and preventive actions.
- Protocol deviation or serious breach reports where a UNSW researcher, staff or student is responsible for the protocol deviation or the serious breach will be reviewed as per the UNSW Research Misconduct Procedure to establish a breach of the UNSW Research Code of Conduct has occurred.
- Protocol deviation or serious breach reports where the UNSW Sponsor's Delegate determines that site personnel are responsible for a protocol deviation or the serious breach will be referred onto their responsible institution for review under their Research Misconduct procedures to establish whether a breach of the Australian Research Code for the Responsible Conduct of Research has occurred.

## 12. Statistics

- Describe the statistical plan for analysing the trial data.

*Data Analysis Plan:* For all primary and secondary outcomes that are normally-distributed and measured over time, a linear mixed model with random effect of individuals will be specified. Fixed effects of time, treatment group and the interaction will be included. Treatment differences at 9 weeks and at 21 weeks and change from baseline to 9 and 21 weeks within each group will be estimated. If the distributional assumption of normality is not tenable, an appropriate transformation of the outcome will be conducted. Alternatively, a generalized linear mixed model with appropriate distribution and link will be used.

The data will be analysed on an intention-to-treat basis. Unadjusted and adjusted analyses will be conducted. Adjusted analyses will include age at baseline and gender. P-values <0.05 will be considered significant.

*MRI Data Analysis Plan:* Quantification of neurotransmitter ratios of the acquired spectra will be analysed using the Java-based magnetic resonance user's interface (jMRUI 6.0, European Union project). To examine differences between periods, 2 Time (Baseline, Post) repeated-measures (RM)-ANOVA on neurotransmitter ratios will be used ( $p < 0.05$ ). Blood oxygen level

dependent (BOLD) imaging, Structural Imaging and Quantitative Arterial Spin Labelling (QASL) will be analysed using Statistical Parametric Mapping (SPM12). Significant differences between periods, 2 Time (Baseline, Post) will be determined using a random effects analysis, false discovery rate,  $p < 0.05$ .

We also aim to determine necessary amendments to the iDBT-Pain skills training based on the qualitative feedback from the interview with the treatment group. This data will be analysed by the investigators and summarised on a form for future development and iterations of the iDBT-Pain intervention.

- Indicate the timing of any planned interim analyses.

There is no planned interim analyses.

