## 10.1 Trial Intervention

- Describe the trial interventions, specify the qualifications and experience required by personnel delegated these responsibilities.

*Trial Intervention:* iDBT-Pain is an online skills training encompassing a total of eight 60-90-minute-long sessions (including an introductory and concluding session), delivered over the internet using Zoom. These sessions will be delivered as part of a group of around 8 to 12 participants and will occur on a Friday lunchtime sometime between 12pm and 2pm AEST approximately every 7 days across eight weeks. For the duration of the eight weeks, and for one week after the concluding Zoom session, participants will have continued access to a web app (iDBT-Pain web app) which participants will access on their own smart device (e.g., iPhone or computer) with their own secure password and username. The iDBT-Pain app includes videos and tasks to encourage skills practice between the Zoom sessions. This intervention is designed to teach DBT skills in mindfulness, emotion regulation, and distress tolerance alongside psychoeducation about chronic pain. Each of the eight session builds on the content of the last to give participants a complete set of skills. This format for the skills training mirrors that used in our successful pilot study where no difficulties in adherence were observed. Nevertheless, to facilitate the completion of all skills by all participants, the iDBT-Pain sessions will be recorded via Zoom. Thus, in the instance that a participant is unable to attend one of the iDBT-Pain sessions they will be sent the session as a recording which they can watch at the earliest opportunity to catch up on the content before the next session. The iDBT-Pain skills training in the current study will follow the study protocol developed and trialled by Norman-Nott et al (2021) and will follow the below session outline:

| Session                       | Module                       | Skills                                                                                                         | Function                                                                                                                                                      |

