*Treatment Condition:* Participants in the treatment condition will receive the iDBT-Pain intervention. The iDBT-Pain intervention involves one 60-90 minute introductory session, six 60-90 minute iDBT-Pain sessions delivered by a DBT skills trainer via Zoom in groups of 8 to 12 participants, and one concluding session delivered weekly (every 7 days) over eight weeks. As part of the iDBT-Pain intervention, for the duration of the eight weeks, and for one week after the concluding Zoom session, participants will have continued access to a web app (iDBT-Pain web app) which participants will access on their own smart device (e.g., iPhone or computer) with their own secure password and username. The iDBT-Pain app includes videos and tasks to encourage skills practice between the Zoom sessions and to maintain the skills in the week

following the concluding session. Participants will be provided with a set of clear instructions to set up the app and to access the sessions (Attachment 9).

*Fidelity and Consistency Across Treatment Groups:* Participants in the treatment condition will be in one of two skills training groups consisting of 12 participants for their iDBT-Pain sessions. The structured protocol (see section 10.1) for the iDBT-Pain sessions will ensure treatment fidelity and consistency across the two groups to mitigate effects of confounding factors that may arise due to different groupings.

*Treatment-as-usual condition:* In contrast to the treatment condition, the treatment-as-usual condition will receive no intervention as part of the trial. Participants in the treatment-as-usual condition may receive treatment options as offered by the healthcare professionals they would normally consult with in the community (see Section 10).

Upon conclusion of the study (e.g, following 3-month assessment) all participants will retain (if in the treatment group) or receive (if in the treatment-as-usual group) access to the iDBT-Pain app for personal use on their own smart device.

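### Only the treatment arm is taught in Zoom groups, but the model has a random effect for individuals alone, so for any positive within-group correlation the 5% type I error is exceeded

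*Protocol*

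**What the plan says.** Section 12 fixes the analysis model for the primary and the repeated secondary outcomes: "a linear mixed model with random effect of individuals will be specified". It continues: "Fixed effects of time, treatment group and the interaction will be included". The covariates are also named: "Adjusted analyses will include age at baseline and gender". The contrasts include "Treatment differences at 9 weeks and at 21 weeks", and the decision rule is "P-values <0.05 will be considered significant". Skills-training group appears in none of these.

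Section 10.1 Trial Intervention says of the Zoom sessions: "These sessions will be delivered as part of a group of around 8 to 12 participants". The description of the treatment condition repeats this: "delivered by a DBT skills trainer via Zoom in groups of 8 to 12 participants". The treatment-as-usual arm gets no trial intervention, so it has no such groups.

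The paragraph on fidelity across treatment groups, in the same section, does address grouping: "The structured protocol (see section 10.1) for the iDBT-Pain sessions will ensure treatment fidelity and consistency across the two groups". It adds that this is meant to mitigate confounding from different groupings, and it describes two groups of 12. Section 6 plans 50 per arm, with a within-subject correlation of 0.2 and no allowance for correlation between members of a group.

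**The concern.** This is a partially nested design. Treated participants share eight weekly sessions, the discussion in them and the other members, so their outcomes may be correlated. Control outcomes have no such source of correlation.

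A random intercept per person accounts for repeated measurements on that person. It says nothing about two different people in one group. If they are positively correlated, the treatment-arm mean varies more than the model allows, and the confidence interval and p-value for the main comparison are too favourable. Section 6 does not count the loss of power either.

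This is not a detail left to an analysis plan: the protocol names the random effect, the fixed effects and the covariates, and together they imply independence.

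**Working it through.** **Inputs from the protocol.** Groups of 8 to 12 (10.1). 50 per arm, effect size d = 0.7, 80% power, alpha 0.05, within-subject correlation 0.2, attrition 15–20% (section 6). Two-sided testing is assumed, as sidedness is not stated. The ICC is not given, so 0.01, 0.05 and 0.10 are assumed.

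**The plan's own sample size.** Section 6 does not name the contrast. One choice that gives 100 is the mean of the two post-baseline visits minus baseline:
- Variance = (1 + 0.2)/2 + 1 − 2 × 0.2 = 1.2.
- n per arm = 2 × (1.96 + 0.84)² × 1.2 / 0.7² ≈ 38.4, so 39, or 40 with the t distribution.
- 40 / 0.8 = 50 per arm, 100 in total.

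A single post-baseline score needs 33–34 per arm before attrition. A simple change score needs 52–53. All of these treat participants as independent.

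**Number of groups.** 50 treated / 12 at most per group = 4.2, so at least five groups. The check uses 5 groups of 10, or 5 of 8 once 20% attrition leaves 40 per arm.

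**Type I error of the stated model.** With group size m:
- design effect in the treatment arm: DE = 1 + (m − 1) × ICC
- variance ratio for the arm difference, equal arms: R = (DE + 1)/2
- actual alpha = 2 × [1 − Φ(1.96/√R)]

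For m = 10:

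| ICC | DE | R | SE too small by factor | Alpha, formula | Alpha, simulated |
|---|---|---|---|---|---|
| 0.01 | 1.09 | 1.045 | 1.02 | 5.5% | 5.4% |
| 0.05 | 1.45 | 1.225 | 1.11 | 7.7% | 7.7% |
| 0.10 | 1.90 | 1.45 | 1.20 | 10.4% | 10.5% |

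The simulation used 100,000 trials per row on a single post-baseline score. By the formula, the extremes of group size at ICC 0.05 are 7.1% (m = 8) and 8.3% (m = 12).

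**Three-visit model as stated.** Simulating the random-intercept model with a group effect after baseline (8,000 trials, 5 groups of 10, ICC 0 / 0.01 / 0.05 / 0.10) gives:
- 9-week difference: 4.9 / 5.9 / 7.9 / 11.3%
- difference in change from baseline: 5.2 / 5.2 / 6.6 / 8.9%

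The individual intercept does not absorb the group effect.

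**Group-aware test.** Compare the mean of the k group means with the control mean. Let v₁ = (variance of group means)/k and v₂ = (control variance)/n. Satterthwaite df = (v₁ + v₂)² / [v₁²/(k − 1) + v₂²/(n − 1)].
- 5 groups of 10: alpha about 5.1–5.5% for ICC 0 to 0.10.
- 5 groups of 8 against 40, d = 0.7, single post-baseline score: power about 82% at ICC 0, 74% at 0.05 and 67–68% at 0.10. At ICC 0 the individual-level test would have about 87%. The gap is the price of few degrees of freedom: with v₁ = v₂, df = 4/(1/4 + 1/39) ≈ 14.5.
- 2 groups of 12, as 10.1 literally says: the group variance rests on 1 df, alpha is about 7–9% and power about 36–52%.

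**The case against.** **The inflation is assumed.** No ICC is given, and several features point to a low one: one trainer for all groups, structured skills teaching that the protocol distinguishes from psychotherapy, individual practice in the app, and recordings for missed sessions. At ICC 0.01 the stated model gives about 5.5% and a group-aware test just over 5%, which is no practical difference. This stands as a limit on size. It does not make the correlation zero, and the protocol neither states nor justifies zero.

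**A reader might infer that a shared recruitment cohort is part of the cause.** The documents do not support that. Randomisation is in blocks of 6 and treatment starts once 24 are randomised, so both arms share the cohort. Simulating a cohort effect common to both arms (5 cohorts, 10 per arm, ICC 0.05 / 0.10) with no group effect gives 4.4% / 4.1%, which is conservative. Only correlation specific to the skills groups inflates the error.

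**A reader might infer that the protocol claims its structured sessions remove the correlation.** It does not. It says that they ensure consistency, with the aim of mitigating confounding. The gap is that nothing statistical accompanies this.

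**The correction may not work.** With two groups it does not work well. That is a reason to settle the number of groups first, not to keep the stated model.

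**Conclusion.** The stated model does not fit the design. For any positive within-group correlation, the standard error of the arm difference is too small and the 5% level is exceeded. The direction is certain; the size is not. With 5 groups of 10, type I error for the 9-week difference runs from about 5.5% (ICC 0.01, negligible) through 7.7% (0.05) to 10.5% (0.10), and is lower for change from baseline.

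It would go too far to say that the trial's error rate is known to be wrong by a given amount, because the documents contain no ICC. The figures also assume equal arms, equal group sizes and two-sided testing. The power figures use a single post-baseline score, and section 6 does not say which contrast it used. For a self-described pilot that nonetheless tests efficacy at 0.05, this should be corrected.

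**What to change.** 1. Reconcile the number of groups. Two groups of 12 (10.1) matches the 48 participants still given in section 5 and in the randomisation procedure. The 50 per arm in section 6 needs at least five groups of up to 12. Settle this first, because the remaining steps depend on it.
2. In section 12, add a random effect for skills-training group in the treatment arm only, with treatment-as-usual participants as singletons, and use Satterthwaite or Kenward-Roger degrees of freedom.
3. Record each treated participant's skills-training group in the dataset.
4. In section 6, name the contrast and restate power over a range of ICC values.

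A fixed effect for recruitment cohort and arm-specific residual variances are optional refinements.

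The cost is wording and one recorded variable; nothing changes for participants. The downside is wider intervals and a group variance estimated imprecisely from about five groups.

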## 6. Sample Size

The plan is to enrol 100 subjects to complete the trial. The nominated sample is based on a sampled size calculation using SAS 9.4 conducted by biostatistician [name] (UNSW Mark Wainwright Analytical Centre). To calculate sample size for the current trial the effect size from our pilot data from the secondary outcome (pain intensity, effect size = .82) (Norman-Nott et al. 2021) has been used as it had a lower effect size than the primary outcome (i.e., emotional dysregulation, effect size = .88). To detect a mean difference of effect size 0.7 between treatment groups in the secondary outcome (i.e., pain intensity), a total of 100 people (50 in each group) will be required. This assumes 80% power, alpha of 0.05 and a within-subjects correlation of 0.2. This aligns with the recommendation for pilot trials in clinical/translational research that states that the number of participants required for a pilot trial is approximately 20-50 per arm (Moore et al., 2011). To account for an expected 15-20% attrition, the total sample size is 100.

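### The planned 9-week comparison makes no use of the baseline DERS-18 score; at the protocol's own correlation the loss is small, but avoidable

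*Protocol*

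**What the plan says.** Section 2 names emotion dysregulation as the primary outcome and the post-intervention assessment as the primary endpoint. Section 10.1 measures it with the DERS-18 in both arms at baseline, post-assessment and 3-month follow-up.

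Section 12 specifies a linear mixed model with a random effect per person. On its terms it says: "Fixed effects of time, treatment group and the interaction will be included". On the estimates: "Treatment differences at 9 weeks and at 21 weeks and change from baseline to 9 and 21 weeks within each group will be estimated". The comparisons between arms are thus the differences at each follow-up visit, and change from baseline is listed only within an arm. Unadjusted and adjusted analyses are both planned, and for the latter: "Adjusted analyses will include age at baseline and gender". Nothing makes the baseline outcome score a covariate, and nothing gives the two arms a common baseline mean.

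Section 6 bases the sample size on an effect of 0.7 in pain intensity: "a total of 100 people (50 in each group) will be required". It adds: "This assumes 80% power, alpha of 0.05 and a within-subjects correlation of 0.2". It also says: "To account for an expected 15-20% attrition, the total sample size is 100".

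Sections 5 and 8 place random allocation after consent and before the baseline assessment.

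**The concern.** Baseline is in the model, so it is easy to assume that the week-9 difference has been corrected for it. It has not. When group, time and their interaction are all free, each arm has its own mean at each visit, and the week-9 contrast simply compares the two week-9 means. The baseline responses do not sharpen that contrast. Adding age and gender does not change this, because neither is the baseline outcome.

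Two things are at stake. The first is precision, which is lost to whatever extent baseline DERS-18 predicts week-9 DERS-18. The second is how the result reads if the arms differ by chance at baseline: part of that difference carries into the reported effect, and no planned analysis removes it.

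**Working it through.** **Inputs.** Effect 0.7 SD, alpha 0.05 (taken as two-sided; the protocol does not say), 80% power, correlation r = 0.2, 50 per arm and attrition of 15-20%, all from section 6. The effect and correlation are stated for pain intensity, and applying them to DERS-18 is an assumption. With 20% attrition, 50 × 0.80 = 40 per arm.

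**Formulas.** n per arm = 2f × ((1.960 + 0.842)/0.7)². Power = Φ(0.7 × √(n/(2f)) − 1.960). The variance factor f depends on the contrast:
- week-9 difference: 1
- difference in change: 2(1 − r)
- week-9 difference adjusted for baseline: 1 − r² (large-sample; estimating the slope gives a little of this back).

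**The protocol's figure of 100.**
- Week-9 difference: 32.04, so 33 per arm and 66 in total; 66/0.85 gives 78 and 66/0.80 gives 83. This is not 100, and the correlation plays no part in it.
- Difference in change, f = 1.60: 51.26, so 52 per arm. At 50 per arm the power is 79.0%, close to the stated 80% but with nothing left for attrition.
- Baseline against the mean of two post visits, f = 1 + (1 + 0.2)/2 − 2(0.2) = 1.20: 39 per arm, 78 in total, and 98 after 20% attrition.

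The figure is therefore approached only through contrasts between baseline and follow-up, which section 12 does not list as comparisons between arms.

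**What the planned model estimates.** In simulated complete-data trials of 100 people (150 at each of r = 0.2 and 0.6), the model's week-9 contrast matched the raw difference in week-9 means to within 3 × 10⁻¹⁵. Its slope on the chance baseline difference was 0.20 and 0.56 respectively. With a common baseline mean imposed, the correlation with baseline imbalance fell to about zero (0.01 and −0.05). The SD of the estimate fell from 0.177 to 0.172 and from 0.190 to 0.154.

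**Size of the loss (effect 0.7).**

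| r | Contrast | Variance factor | Power, 50 per arm | Power, 40 per arm |
|---|---|---|---|---|
| 0.2 (protocol) | Week-9 difference, as listed | 1.00 | 93.8% | 87.9% |
| 0.2 | Adjusted for baseline | 0.96 | 94.7% | 89.2% |
| 0.2 | Difference in change | 1.60 | 79.0% | 69.7% |
| 0.5 (assumed) | Adjusted for baseline | 0.75 | 98.1% | 95.1% |
| 0.7 (assumed) | Adjusted for baseline | 0.51 | 99.8% | 99.2% |

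The week-9 difference keeps its factor of 1.00 at every r. Since 1 − r² = (1 − r)(1 + r), and 1 + r is at most 2, the adjusted factor never exceeds 1 or 2(1 − r).

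**Imbalance.** One standard error of the baseline difference at 50 per arm is √(2/50) = 0.2 SD. It moves the week-9 difference by r × 0.2: 0.04 SD at r = 0.2, and 0.12 SD at an assumed r of 0.6. A difference in change would over-correct by (1 − r) × 0.2 = 0.16 SD at r = 0.2.

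**The case against.** The best defence is that, for the contrast section 12 actually lists, the protocol's own correlation leaves little to gain: 4% of variance and about one power point. This is a self-described pilot, and randomisation keeps the unadjusted test valid, since chance imbalance is not bias. All of that stands. With missing follow-up the mixed model also borrows some information from baseline, so the equality with raw means is exact only for complete data.

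The timing objection also stands. If people know their allocation when they answer at baseline, and that shifts answers by δ SD between arms, an adjusted estimate is displaced by about r × δ. As an illustration, δ = 0.2 gives 0.04 SD at r = 0.2 and 0.14 SD at r = 0.7. The raw week-9 difference is not displaced in this way. The precision advantage therefore depends on baseline answers being unaffected by allocation.

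A reader might infer that the plan loses its stated power, because a difference in change has 1.60/0.96 = 1.67 times the variance of the adjusted comparison and 69.7% power at 40 per arm. The document does not support that. Section 12 does not list that comparison between arms, and the drop from 79.0% to 69.7% arises because section 6 uses 100 both before and after attrition, which is a separate matter.

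A reader might also infer that planning unadjusted and adjusted models gives two chances of success, or that the random effect forces equal correlation across visits. Section 12 does not say that either model alone would suffice, and it does not rule out a further residual covariance. Both are details that an analysis plan, not shown here, could settle.

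The omission of baseline is different in kind, because the protocol itself fixes the model, the contrasts and the adjusting covariates.

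**Conclusion.** The point holds in a limited form. As written, the primary comparison makes no use of baseline DERS-18 and carries chance baseline imbalance. At r = 0.2 the cost is 4% of variance, about one power point at 40 per arm, and 0.04 SD of shift for a one-standard-error imbalance. It becomes material only if the true correlation is higher: a 25% to 49% variance reduction at 0.5 to 0.7, values the protocol does not give. Were the group-by-time interaction used as the test instead, adjustment would still be at least as precise (0.96 against 1.60 at r = 0.2).

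These figures assume a two-sided test, complete data, section 6's pain-intensity inputs carried over to DERS-18, and baseline answers unaffected by allocation. This is a worthwhile and inexpensive improvement. It does not show that the trial is underpowered or its planned test invalid.

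**What to change.** In section 12, name as the primary analysis the difference between arms in DERS-18 at 9 weeks adjusted for baseline DERS-18. Baseline can enter as a covariate, or a longitudinal model can give both arms a common baseline mean. Report the models without baseline adjustment as supportive.

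State the assumption that knowledge of allocation did not affect baseline answers. Where possible, have the baseline questionnaire completed before allocation is disclosed, and amend sections 5 and 8 to say so. Where that is not possible, keep the unadjusted week-9 difference as a sensitivity analysis.

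The analysis change costs wording only, since baseline DERS-18 is already collected in both arms. Moving the questionnaire ahead of disclosure is a procedural change to the order of steps, and it needs no extra visits, measures or participants.

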## 2. Trial Objectives and Purpose

- Describe the aim(s) of the clinical trial and specify the research questions that the trial will address.

In a recent pilot study (ethics approval: HC2001990) using a single-case experimental design ( $N=3$ ) evidence was promising for the feasibility and acceptability of an online skills training for people in chronic pain (internet-delivered dialectical behavioural therapy skills training; iDBT-Pain) (Norman-Nott et al., 2021).

The purpose of the current pilot trial is to further investigate the effectiveness of iDBT-Pain for individuals with chronic pain to determine the effects on the emotional, sensory, and neurological components associated with chronic pain. The objectives of this trial are to:

1. Reduce emotion dysregulation
2. Reduce pain intensity
3. Improve psychological factors associated with chronic pain (e.g., symptoms of anxiety and depression, harm avoidance traits, sleep quality, life satisfaction, and coping behaviours)
4. Conduct exploratory investigation of changes in brain function (e.g., neurochemical levels in the medial prefrontal cortex)

We additionally aim to attain qualitative data to optimise the design of the intervention to provide crucial information for funding to facilitate future development and testing in a full-scale randomised controlled trial.

- Specify the primary endpoints and the secondary endpoints to be measured during the trial.

Participants will be randomly assigned to either a 'treatment' or 'treatment-as-usual' condition. It is hypothesised that participants in the 'treatment' condition will demonstrate a significant improvement in the primary outcome (emotion dysregulation) and secondary outcomes (pain intensity, symptoms of anxiety and depression, harm avoidance, sleep quality, life satisfaction, coping behaviours and social cognitive skills) when measured at post-assessment (primary endpoint) following the 9-week intervention, and this will remain when measured at 3-month follow-up (secondary endpoint).

A further secondary outcome is change in cortical function (e.g., changes in neurotransmitters' levels) which will be observed using magnetic resonance imaging at baseline and post assessment. A semi-structured interview will be used to gather information about participants experience of the skills training during the post-assessment.

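### The neurotransmitter ratios are assigned a two-level repeated-measures ANOVA, which in its standard form uses only participants with both scans; a time-only mixed model would use every scanned participant, for a small gain

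*Protocol*

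**What the plan says.** Section 2 of the protocol adds the imaging measure to the list of outcomes: "A further secondary outcome is change in cortical function", with neurotransmitter levels as the example, observed at baseline and post-assessment. The fourth objective in the same section describes the brain-function work as exploratory.

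Section 12 opens with a general rule: "For all primary and secondary outcomes that are normally-distributed and measured over time, a linear mixed model with random effect of individuals" will be specified. It continues: "Fixed effects of time, treatment group and the interaction will be included". The estimates wanted are also listed: "Treatment differences at 9 weeks and at 21 weeks and change from baseline to 9 and 21 weeks within each group will be estimated". If normality fails, the rule turns to a transformation or a generalised linear mixed model. The section adds: "The data will be analysed on an intention-to-treat basis".

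A separately labelled MRI plan then follows in section 12. For the spectroscopy data it says: "2 Time (Baseline, Post) repeated-measures (RM)-ANOVA on neurotransmitter ratios will be used". It does not say how a participant with only one usable scan is handled, or whether this is meant as an exception to the general rule.

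Section 7.4 and the brain imaging paragraph under the heading 10.1 Trial Intervention restrict scanning to treatment-arm participants who are eligible and wish to take part, at two time points.

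**The concern.** A two-level within-person ANOVA on time is algebraically a paired t-test (F equals t squared). In its usual form it needs both measurements, so a participant with a baseline scan but no post scan contributes nothing.

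Missing second scans are foreseeable. Section 6 allows for dropout: "To account for an expected 15-20% attrition, the total sample size is 100". Section 7.6 ends data collection on withdrawal. Scans are done in person in Sydney (section 8), and a participant may stop a scan at any time (section 9).

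Two things are at stake. The estimate of change is somewhat less precise than it could be. It is also unbiased for all scanned participants only if those who miss the second scan do not differ systematically from those who return. A mixed model for the same change uses all scans and remains valid when loss depends on the observed baseline value, provided its covariance structure is about right.

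**Working it through.** The protocol gives no scan number, SD, effect size or power for spectroscopy, so there is no stated figure to reproduce. The check compares the two estimators.

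**Inputs**
- Loss of second scans: 15-20%, borrowed from the trial-wide attrition in section 6. The share with both scans is f = 0.85 to 0.80.
- Within-person correlation r: 0.2, borrowed from section 6, where it serves the sample-size calculation. No value is given for neurotransmitter ratios, so a range up to 0.7 is shown.
- Equal variances at the two times, set to 1 (assumption).
- Baseline gap between non-returners and returners: 0.5 SD (illustrative only).

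**Step 1: complete pairs.** In one simulated data set of 20 participants with both scans, the mixed model and the paired analysis gave the same estimate (-0.0097) and the same standard error (0.1877).

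**Step 2: precision with missing second scans.** Let n participants have both scans and N = n/f have a baseline scan.
- Paired analysis: variance of the mean change = 2(1 - r)/n.
- Likelihood (mixed-model) estimate: post mean of the pairs + r × (baseline mean of all - baseline mean of the pairs) - baseline mean of all. Its variance is (1 - r²)/n + (1 - r)²f/n.
- Ratio of the second to the first: [(1 + r) + (1 - r)f]/2. The number scanned cancels.

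| r | f = 0.85 | f = 0.80 | Reduction in variance |
|---|---|---|---|
| 0.2 | (1.2 + 0.68)/2 = 0.94 | (1.2 + 0.64)/2 = 0.92 | 6-8% |
| 0.5 | (1.5 + 0.425)/2 = 0.963 | (1.5 + 0.40)/2 = 0.95 | 4-5% |
| 0.7 | (1.7 + 0.255)/2 = 0.978 | (1.7 + 0.24)/2 = 0.97 | 2-3% |

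On the standard-error scale this is about 1-4%, since √0.978 = 0.989 and √0.92 = 0.959. In the simulated example with 4 of 20 post scans removed, the paired analysis kept 16 people (standard error 0.2086), and the mixed model kept 20 people and 36 scans (0.2069).

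**Step 3: bias when loss depends only on baseline.** The bias of the complete-pair change is (r - 1) × (baseline mean of returners - baseline mean of all). With a 0.5 SD gap, the bracket is 0.5 × (1 - f) = 0.075 to 0.10 SD.
- r = 0.2: 0.8 × 0.075 to 0.8 × 0.10 = 0.06 to 0.08 SD in size.
- r = 0.7: 0.3 × 0.075 to 0.3 × 0.10 = 0.02 to 0.03 SD.

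A simulation with 20% loss and r from 0.2 to 0.8 gave zero bias when loss was unrelated to baseline, and 0.02-0.08 SD when the log-odds of loss rose by 0.5 per baseline SD.

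**The case against.** A reader might infer that section 12 contradicts itself by naming two analyses for one outcome. The documents do not support that. The general model contains a treatment-group effect, a group-by-time interaction and contrasts at 21 weeks. With no control-arm scans and no 21-week scan, none of these can be estimated for spectroscopy. The rule is also limited to outcomes that are normally distributed and measured over time. The separately labelled MRI plan can fairly be read as a specific rule that takes precedence. What remains is that the protocol does not say so.

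A reader might also infer a breach of the intention-to-treat commitment. That principle protects a comparison of arms as randomised. This is an optional before-after measurement in one arm, with no such comparison to protect.

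The protocol nowhere states that single scans are discarded. That follows from the standard form of the named method, and handling of missing scans could be left to a statistical analysis plan that is not shown here. The choice of method, however, is already fixed in the protocol.

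Three further points stand. The gain is small, and its size rests on borrowed inputs. A paired test has exact degrees of freedom under normality, whereas a mixed model with missing scans needs an approximation. Section 2 also describes the objective as exploratory, although it names the measure a secondary outcome.

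**Conclusion.** The point holds as a cheap improvement, not as the correction of an error. For a named secondary outcome, the protocol picks a method that in its standard form ignores participants with a single scan, where a time-only mixed model would use them.

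Under 15-20% loss of second scans and equal variances, the variance of the mean change falls by about 6-8% at correlation 0.2 and 2-3% at 0.7. Under the illustrative 0.5 SD baseline gap, the bias avoided is about 0.06-0.08 SD at correlation 0.2 and 0.02-0.03 SD at 0.7. If every scanned participant returns, nothing changes. The loss rate and the lower correlation come from the sample-size section, not from imaging data, so these figures are a range and not a forecast. The randomised comparison of the questionnaire outcomes is not affected.

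**What to change.** In section 12, replace the sentence on the repeated-measures ANOVA with:

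> Neurotransmitter ratios will be analysed in scanned treatment-arm participants with a linear mixed model (random effect of individual, fixed effect of time: baseline, post; small-sample degrees of freedom, e.g. Kenward-Roger), including every participant with at least one usable scan; this replaces the general group-by-time model for this outcome.

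The last clause also settles how the MRI plan relates to the general rule. The SPM12 analyses can stay as they are. If the team prefers to keep the ANOVA, it should at least state that the MRI plan is an exception to the general model and how single scans are handled.

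The cost is one sentence, with no extra data, scans or staff. The downside is an approximate instead of an exact degrees-of-freedom calculation when scans are missing.
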